#### Acceptability

The participants acceptability of intervention will be assessed by (1) adherence rate, (2) adverse events, and (3) participants’ satisfaction will be assessed by brief open-ended question about suggestions on the improvements of intervention.

### Sample size

The sample size calculation was performed using the Power Analysis and Sample Size (PASS) software (NCSS, Kaysville, Utah). Parenting self-efficacy was chosen as the primary outcome for sample size calculation. According to a study using the C-PSOC to evaluate the effects of psychoeducational therapy on parenting self-efficacy in parents of children with ASD, the mean ± standard deviation (*SD*) of average total parenting self-efficacy was reported as 6.99 (0.76) (26). Considering a 15% dropout rate and α = 0.05 (two-sided), PASS indicated that a total of 80 participants (40 participants in each group) would be required to achieve 80% power.

$$n_{1\;}=\;n_{2}\;=\;2\times [\frac{{\left(t_{\alpha }\;+\;t_{\beta }\right)}^{2}\;\times \;s^{2}}{\delta^{2}}]$$

### Statistical methods

IBM SPSS 26.0 (IBM Corp., NY, USA) will be used for data analysis. Descriptive statistics such as mean, median, standard deviation, interquartile range, frequency, and percentage will be used to describe the baseline characteristics of the participants. The independent *t*-tests and one-way ANOVA will be used to compare the homogeneity of the two groups at baseline. Outcome analyses will be conducted based on the intention-to-treat (ITT) principle. Missing data will be imputed based on the results of Little’s missing completely at random (MCAR) test. The generalized estimating equations (GEE) model will be used to analyze the group and time differences in outcome variables. Potential covariates such as sociodemographic or clinical characteristics with a *P<*0.01 in the baseline will be considered in the adjusted GEE model. Open-ended contents will be summarized descriptively with selected anonymized quotations. Statistical significance will be set at 0.05 (two-sided).

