### Data collection

The researcher will recruit parents by posting posters during the first two days of hospitalization. Eligible parents will undergo a thorough explanation of the study, and written consent will be obtained (-T1) by researchers. Two nurses trained in using standardized instructions will collect the data. Baseline data (T0) will be collected face-to-face using a paper version of the questionnaire. Post-intervention data will be collected within three days after intervention (T1) and 6 months after the intervention (T2) through the online questionnaire platform, *Questionnaire Star* (Changsha Ranxing Information Technology Co., Ltd). This platform was chosen for its ability to ensure data quality, provide an opt-out option, and allow parents to complete the surveys at their convenience. The flow diagram of the trial procedures is presented in **Figure 2**.

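### Imputation of missing outcomes is steered by Little's MCAR test, a weak guide with about 12 dropouts; the imputation method should not depend on its result

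*Protocol article*

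**What the plan says.** The Statistical methods section of the protocol article sets three things that bear on missing outcomes.

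- Population: "Outcome analyses will be conducted based on the intention-to-treat (ITT) principle".
- Missing values: "Missing data will be imputed based on the results of Little’s missing completely at random (MCAR) test".
- Model: "The generalized estimating equations (GEE) model will be used to analyze the group and time differences in outcome variables". No weighting for dropout is mentioned.

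The section does not say what a significant or a non-significant test triggers. The Sample size section plans "a total of 80 participants (40 participants in each group) would be required to achieve 80% power" and allows for 15% dropout. Under Withdrawal criteria, a parent who misses the post-intervention evaluation counts as withdrawn, so the intention-to-treat analysis depends on how that parent's missing values are handled.

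**The concern.** Little's test compares the means of the observed values between missingness patterns. It never sees the missing values. A non-significant result in a small trial is therefore weak evidence that data are missing completely at random, and a significant result does not show that they are missing at random. A rule that lets this result choose the imputation rests on information the test does not give.

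The model raises the stakes. Unweighted GEE on the observed data generally needs MCAR, apart from missingness explained by covariates in the model. After proper multiple imputation under MAR it needs only MAR. If a non-significant test is taken as licence to skip imputation, or to use a simple fill-in, any bias from dropout stays in the estimate.

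The design makes it plausible that dropout differs somewhat by arm. The arms are not randomised and were recruited one after the other (Study setting and population). Participants are not blinded (Limitations). Only the intervention arm attends four sessions. T1 and T2 are online self-report, and T2 comes six months after the intervention.

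**Working it through.** **Inputs from the article.** N = 80, 40 per arm; dropout 15%; 80% power; two-sided alpha 0.05; assessments at T0, T1 and T2.

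**The plan's own figure.** The 80 cannot be reproduced because the difference δ is not stated, but it can be solved for:

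- Evaluable per arm: 40 × 0.85 = 34. Expected dropouts: 80 × 0.15 = 12, about 6 per arm.
- Implied standardised difference: (1.96 + 0.84) × √(2/34) = 2.80 × 0.2425 = 0.68 SD. On the stated SD of 0.76 this is 0.68 × 0.76 = 0.52.
- Standard error of a difference in means with 34 per arm: √(2/34) = 0.24 SD.

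These two values serve only as yardsticks for bias.

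**Assumptions not in the article.** Three visits with within-person correlation 0.5. Dropout follows logit(p) = a − b × score in SD units, with a set to give 15% overall and b = 0.5, 0.8 or 1.0. These slopes are odds ratios of exp(0.5) = 1.65, exp(0.8) = 2.23 and exp(1.0) = 2.72 per SD lower score. Under MAR the score is the baseline value; under MNAR it is the unseen T2 value.

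**Test statistic.** d² = Σ n_j (ȳ_j − μ̂_j)ᵀ Σ̂_j⁻¹ (ȳ_j − μ̂_j), summed over missingness patterns j, with EM estimates of mean and covariance. It is referred to chi-square with Σp_j − p degrees of freedom, at the 0.05 level.

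**Results at n = 80, 15% dropout, correlation 0.5.**

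| Dropout mechanism | Test rejects MCAR | Bias in group difference at T2, observed cases |
|---|---|---|
| MCAR | about 4% | none expected |
| MAR, same in both arms, b = 0.5 / 0.8 / 1.0 | about 21% / 48% / 65% | about 0 |
| MNAR, same in both arms | about 10-22% | up to about −0.07 SD, towards the null |
| Opposite directions by arm, MAR or MNAR | about 4-9% | about 0.07-0.26 SD |

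The opposite-direction case is the worst for the test because it pools the arms: low scorers leaving one arm and high scorers leaving the other cancel in the pattern means. The sign of the bias depends on which arm loses its low scorers. Running the test within each arm would leave about 6 dropouts in each.

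**Second set of assumptions** (correlation 0.6, dropout split between T1 and T2, odds ratios 1.5 / 2 / 3 per SD):

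- 15% dropout, C-PSOC only: rejection 14% / 39% / 73% under MAR and 7% / 17% / 34% under MNAR.
- 15% dropout, four outcomes entered together: 10% / 20% / 44% under MAR.
- 25% dropout, C-PSOC only: 22% / 58% / 92% under MAR.
- Opposite-direction MNAR dropout: rejection about 2-5% throughout, with completer bias 0.09-0.24 SD at 15% dropout and 0.16-0.39 SD at 25%.

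Rejection under MCAR was 4-6%, so the test holds its size and the low detection is not an artefact.

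**Scale.** At 15% dropout and correlation 0.5, 0.07/0.68 = 10% and 0.26/0.68 = 38% of the implied design difference. In standard errors, 0.07/0.24 = 0.3 and 0.26/0.24 = 1.1.

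**The case against.** The strongest reply is that the harmful branch is not in the text. The sentence says missing data will be imputed, with the test as a guide. A reader might infer that a non-significant test leads to GEE on the observed cases; the article does not say so. If multiple imputation under MAR followed either result, GEE would no longer need MCAR. This stands, so the bias can only be put conditionally.

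A second stronger reading is that undetected dropout dependence will in general distort the primary comparison. The figures do not support it. With the same mechanism in both arms, bias in the group difference is about zero under MAR and at most about 0.07 SD, towards the null, under MNAR, against a standard error of 0.24 SD. Material bias needs dropout that differs by arm. The design makes some difference plausible, but the article does not show one.

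A third is that the test would miss nearly everything. It would not: steep MAR dependence is found in about 65-73% of trials at 15% dropout and in 92% at 25% when C-PSOC is tested alone.

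Finally, the imputation model, the number of imputations and the sensitivity analyses may properly sit in an analysis plan not shown here. Their absence is not criticised. What remains is a choice the article does make: the test result steers imputation. An analysis plan that followed that sentence would inherit the weakness.

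**Conclusion.** The concern holds as a fault in the decision rule, not as a demonstrated bias in the primary result. With about 12 dropouts, non-rejection is not evidence of MCAR, and rejection does not tell MAR from MNAR. Except under steep MAR dependence, a non-significant result is the more likely one, and it is almost certain in the opposite-direction case where bias is largest.

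The consequence depends on two things the article does not settle: what is done after a non-significant test, and whether dropout works differently in the two arms. The upper end of the bias, about 0.26 SD at T2 with 15% dropout, belongs to a deliberately extreme case. The correlations, slopes and split of dropout between visits are assumptions. The weakness of the test was seen under both sets of them; its exact size was not the same. The point should be corrected but does not by itself invalidate the design.

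**What to change.** Remove the test as a decision rule. State that, whatever Little's test shows, missing outcomes will be multiply imputed under MAR and the GEE estimates pooled. Keep the imputation model small, with arm and the T0, T1 and T2 values of the outcome, because only about 6 parents per arm are expected to have missing data. A likelihood-based mixed model on all available data is an acceptable alternative.

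Report Little's test descriptively only. Add one delta-adjusted sensitivity analysis, for example with imputed intervention-arm values made worse, because imputation under MAR does not remove MNAR bias.

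The cost is a change of wording and modest extra programming, with no new data. By the stated study dates, data collection ended in May 2024. The change should therefore be fixed before outcomes are analysed or, failing that, dated and reported as made afterwards.

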Emerging studies have demonstrated that health education based on self-efficacy theory has been effective in increasing parental self-efficacy and improving disease management outcomes for parents of children with chronic diseases (27–29). For example, Cheng et al. (27) designed a randomized controlled trial (RCT) based on the self-efficacy theory for parents in controlling child’s eczema, which showed significant improvement in the child’s eczema severity and parental self-efficacy. Similarly, another RCT was conducted for parents of children with asthma, the intervention groups had significantly higher parental self-efficacy and 1.4 times the child’s experience of an asthma crisis improved compared to the control group post-intervention (da Rocha Mendes et al., 2024). However, non-significant results were also observed, an online platform was developed to enhance parental self-efficacy and of parents with a child with type 1 diabetes, the self-empowerment was not significant change post-intervention (30).

In summary, most existing ASD parents program emphasize knowledge or skills delivery (10), but relatively few have been designed primarily to enhance parental psychological such as PSE, or to target Bandura’s four sources of self-efficacy in a structured way (3). Therefore, this intervention will address the gap by testing whether a theory-driven, nurse-delivered PSE intervention improves parental self-efficacy, parenting stress, family quality of life and symptom severity post intervention and at 6-month follow-up. The hypotheses are as follows:

Compared with the control group, the intervention group will be expected to demonstrate higher parental self-efficacy scores at post-intervention and at 6-month follow-up.Compared with the control group, the intervention group will show higher improvements in secondary outcomes at post-intervention and at 6-month follow-up, including lower parenting stress, higher treatment compliance, family quality of life, and reduced child symptom severity.

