#### Primary outcome

Parental self-efficacy will be measured using the Chinese version of the Parenting Sense of Competence Scale (C-PSOC) (33). The 6-point rating scale comprises a 17-item and assesses satisfaction and efficacy across two dimensions. Scores range from 17 to 102, with higher scores indicating higher levels of parenting self-efficacy. The C-PSOC has demonstrated high internal consistency and reliability (34).

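### The planned GEE names neither the contrast nor the time point that decides the primary hypothesis, and does not assure baseline C-PSOC in the model

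*Protocol article*

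**What the plan says.** The Statistical methods section gives the outcome model in one sentence: the GEE "model will be used to analyze the group and time differences in outcome variables". It names no interaction, contrast or reference visit. Sociodemographic or clinical characteristics are candidates for the adjusted model when they differ between groups at baseline with P<0.01. Baseline C-PSOC is not named as a covariate. The error level is set once, for everything: "Statistical significance will be set at 0.05 (two-sided").

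Hypothesis 1, at the end of the Introduction, reads: "the intervention group will be expected to demonstrate higher parental self-efficacy scores at post-intervention and at 6-month follow-up". Table 1 schedules the PSOC at T0, T1 and T2. The Primary outcome section names the instrument but no visit.

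The Sample size section uses a two-group formula for a single comparison ("Considering a 15% dropout rate and α = 0.05 (two-sided")) with 80% power, giving 40 per group. Under Study setting and population, groups are assigned by calendar period: October 2022 to March 2023 control, April to October 2023 intervention. The Limitations section concedes that baseline imbalance is possible and relies on covariate-adjusted GEE to deal with it.

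**The concern.** Hypothesis 1 is a between-group claim at two follow-up visits. Neither effect that the model sentence names answers it directly. A time difference is not an intervention effect. A group difference taken over all three visits includes T0, before any intervention was given.

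In a randomised trial this would mainly dilute the effect. Here groups are formed by period, so a group main effect also picks up any baseline difference in C-PSOC. The covariate rule gives no assured protection against that.

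Separately, two visits carry the primary hypothesis, the sample size pays for one comparison, and nothing says whether one or both must succeed. The deciding test could therefore be chosen after the results are known.

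**Working it through.** **Inputs from the protocol.** SD 0.76, two-sided α 0.05, 80% power, 15% dropout, 40 per group (Sample size); three C-PSOC visits (Table 1). **Assumed, because not given:** the difference δ, the within-parent correlation r (0.3 to 0.8), equal variances and an exchangeable correlation.

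**1. The plan's own figure.** The formula is n per group = 2(t_α + t_β)² s²/δ². No δ is stated, so N = 80 cannot be reproduced directly. Back-solving: 40 × 0.85 = 34 evaluable per group, and √(2/34) = 0.2425. Then δ = 0.76 × 2.802 × 0.2425 = 0.52, so d is about 0.68 (normal) or 0.69 (t). Check: 2 × 2.802² × 0.76²/0.52² = 33.5, so 34; 34/0.85 = 40; total 80. The sample size therefore fits one comparison at one visit at the full 0.05. With d = 0.69, that comparison has z = 0.69/0.2425 = 2.845 and power Φ(2.845 − 1.960) = 81%.

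**2. Literal reading: group main effect over T0, T1 and T2, effect sustained.**
- Coefficient: (0 + 0.69 + 0.69)/3 = 0.46, two thirds of d.
- SE: 0.2425 × √((1 + 2r)/3).
- Group × time (T1 − T0) has SE 0.2425 × √(2(1 − r)). The T1 difference adjusted for baseline has SE 0.2425 × √(1 − r²). Both estimate d = 0.69 when there is no baseline gap.

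| r | SE of main effect | Power, main effect | Power, T1 − T0 | Power, baseline-adjusted T1 |
|---|---|---|---|---|
| 0.3 | 0.177 | 74% | 67% | 85% |
| 0.5 | 0.198 | 64% | 81% | 91% |
| 0.7 | 0.217 | 56% | 96% | 98% |

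If the effect halves by T2, the main-effect coefficient is (0 + 0.69 + 0.345)/3 = 0.345 and its power is 50/41/36%.

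**3. Baseline gap, no treatment effect.** A gap b that persists at all three visits enters the main effect in full. The rejection probability is Φ(b/SE − 1.960) + Φ(−b/SE − 1.960). For b = 0.3 SD, b/SE is 1.69/1.51/1.38, giving 40/33/28% at r = 0.3/0.5/0.7. The T1 − T0 contrast removes such a gap.

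**4. Two visits under one 0.05 level (bivariate normal, unadjusted comparisons).**
- Either suffices: family-wise error is 9.5/9.1/8.3/7.8% at r = 0.3/0.5/0.7/0.8, and 9.75% if independent.
- Both required: no inflation of α. With d = 0.69 at each visit (81% power each), joint power is 68/70/73% at r = 0.3/0.5/0.7. With exactly 80% each it is 67/69/71%.

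**The case against.** The strongest reply is that the model sentence is loose shorthand. It lists no model terms, does not exclude an interaction and does not say that T0 is an outcome row. Hypothesis 1 speaks of the follow-up visits and hypothesis 2 of greater improvements, both of which point towards a group-by-time reading. A condensed article may also leave model terms to a fuller document.

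This stands to a degree. A reader might infer that the plan has chosen main effects over the interaction; the text does not support that, and the dilution and bias figures are conditional on a literal reading. A reader might also infer that the trial's type I error is 8–9.5%. That needs a rule that either visit suffices, which the protocol never states, and the word joining the two visits in hypothesis 1 can mean that both are required. Nor does the main effect always lose power against the change contrast: at r = 0.3 the order reverses (74% against 67%).

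The reply does not remove the point. The article does state the effects of interest, the covariate rule, the two-visit hypothesis and the single error level. Taken together they leave the deciding test open, and the covariate rule does not assure baseline C-PSOC.

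**Conclusion.** The point holds as a failure to fix the primary test, not as proof that a wrong model was chosen. The protocol names no deciding contrast, no primary time point and no rule for combining T1 and T2, while its sample size is for one comparison.

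What is at stake depends on how the text is applied. With a group main effect including T0, the effect falls to two thirds, power is about 74/64/56% at r = 0.3/0.5/0.7, and a persistent 0.3 SD gap without any effect gives about 40/33/28% false positives. With either visit sufficient, family-wise error is about 8–9.5%. With both required, α holds but power for unadjusted comparisons is about 68–73%, below the stated 80%.

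The power figures rest on the back-solved d = 0.69 and a sustained effect. All of the main-effect figures rest on 34 evaluable per arm, equal variances and an exchangeable correlation.

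**What to change.** State the primary analysis as a GEE of C-PSOC at T1 and T2, with baseline C-PSOC always included whatever its baseline P value, plus group, visit and group × visit. If T0 is kept as an outcome row, the test must be the group × time term, not a main effect.

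Then either name one primary time point (for example T1, with T2 tested only if T1 is significant) or state that both are required and restate the power. Use the analogous baseline-adjusted contrast for the secondary outcomes. For the ABC this can be at T2 only, because Table 1 does not schedule it at T1.

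The cost is a few sentences and no new data; under the ordered option, the second time point becomes conditional on the first. Choose between the two model forms in advance, because they can differ when baselines differ. Adjusting for baseline leaves (1 − r) of a stable gap: for 0.3 SD, that is 0.21/0.15/0.09 SD at r = 0.3/0.5/0.7. The change contrast removes it but has less power. Neither removes secular trends between the two recruitment periods.

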### Limitations

This study has several limitations. First, this study uses a non-randomized design due to high contamination risk and operational constraints in a single ward. This may increase bias to unbalanced baseline characteristics and susceptibility to secular trends. We will mitigate this via standardized delivery and covariate-adjusted GEE models. Second, the study was conducted at a single center, which may limit the generalizability of the findings to a broader population of parents of children diagnosed with ASD. Third, blinding the intervention practitioners and participants is not feasible due to the nature of the health education program. To mitigate potential bias, data analysts will be blinded. Fourth, this study has not conducted in-depth semi-structured interviews, future studies need to incorporate a planned qualitative interview to deepen understanding of intervention effects.

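### Covariates enter the adjusted GEE on a baseline test at P<0.01, a rule that at 40 per group usually leaves out moderate imbalances between the two recruitment periods

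*Protocol article*

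**What the plan says.** Under Study setting and population, parents recruited from October 2022 to March 2023 are controls and those recruited from April to October 2023 receive the programme. Allocation is therefore by calendar period.

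The Statistical methods section compares the groups at baseline first: independent t-tests and "one-way ANOVA will be used to compare the homogeneity of the two groups at baseline". A GEE "model will be used to analyze the group and time differences in outcome variables". Potential covariates, sociodemographic or clinical, with a P value below "0.01 in the baseline will be considered in the adjusted GEE model". No covariate is named for adjustment regardless of its P value, and the model term that carries the treatment effect is not named.

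The Limitations section acknowledges that the non-randomised design risks unbalanced baseline characteristics and secular trends, and answers: "We will mitigate this via standardized delivery and covariate-adjusted GEE models".

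The Sample size section states that "a total of 80 participants (40 participants in each group) would be required to achieve 80% power", allowing for 15% dropout.

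**The concern.** Standardised delivery controls how the programme is given, not who was recruited in each period. Of the two mitigations offered, only covariate adjustment can act on differences in measured characteristics between the groups, and entry to that adjustment is decided by a significance test.

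A baseline P value mixes the size of the imbalance with the sample size and carries no information on whether the variable predicts the Parenting Sense of Competence score. At this sample size a strict 0.01 threshold tends to leave out a prognostic factor with a moderate imbalance, and it can admit an irrelevant factor with a large chance imbalance. At stake is avoidable bias, with an inflated false-positive rate, in the primary group comparison.

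**Working it through.** **Inputs from the protocol.** 40 per group; 15% dropout, so 40 × 0.85 = 34 evaluable per group; entry threshold P<0.01; outcome tests at two-sided 0.05. The protocol gives no expected imbalance and no covariate–outcome correlation, so those below are assumptions. The Sample size section states no target difference, so the 80 can only be back-solved, and the bias is not expressed as a share of a planned effect.

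**Step 1: observed difference needed to pass.** For a two-sample t-test the minimum standardised difference is t(0.995; 2n−2) × √(2/n).
- n = 40: 2.640 × √(2/40) = 0.59.
- n = 34: 2.652 × √(2/34) = 0.64.
- Binary factor at 20/40 in one group, chi-square without continuity correction: 31/40 in the other gives P = 0.0105 and 32/40 gives P = 0.0049. It passes only when 50% faces 80%.

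**Step 2: chance that a truly imbalanced covariate passes.** Noncentral t with noncentrality d√(n/2), tested at 0.01:

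| True imbalance (SD) | 40 per group | 34 per group |
|---|---|---|
| 0.2 | 4.5% | 3.9% |
| 0.3 | 10% | 8.5% |
| 0.4 | 20% | 17% |
| 0.5 | 35% | 29% |
| 0.6 | 52% | 44% |
| 0.8 | 82% | 74% |

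At 40 per group the break-even point is about 0.59 SD. Below it a covariate is more likely to be left out than to pass.

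**Step 3: effect on the group comparison.** Simulation of the rule itself: test the covariate, adjust if P<0.01, otherwise do not. Assumptions: one normally distributed confounder, post-intervention scores compared, no treatment effect, 40 per group, at least 10,000 replicates per scenario.

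| Imbalance (SD) | Correlation with outcome | Bias under the rule (SD) | Type I error, rule | Type I error, always adjusted |
|---|---|---|---|---|
| 0.3 | 0.5 | 0.11 | 7% | 5% |
| 0.4 | 0.4 | 0.10 | 7% | 5% |
| 0.5 | 0.5 | 0.12 | 9% | 5% |
| 0.8 | 0.5 | 0.04 | 7% | 5% |

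The bias is smaller at 0.8 SD than at 0.5 SD because the larger imbalance is usually detected and adjusted for. With 34 per group, the 0.4/0.4 case gives a bias of about 0.11 SD and a type I error of about 7%.

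**Step 4: dependence on the effect term.** Table 1 schedules the primary outcome at T0, T1 and T2 in both groups. If the effect is a group-by-time contrast including T0, a confounder that shifts all time points equally cancels: simulating the 0.4/0.4 case with a T1-minus-T0 contrast gave a bias of about 0 and a type I error of 5%. A confounder that alters change from T0 does not cancel.

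**The case against.** **Repeated measures may already remove much of the confounding.** This is the strongest reply, and it stands in part. A contrast including T0 would cancel stable confounders, but the protocol does not say that the effect is read this way. Confounders of change would remain in any case; child age, time since diagnosis and prior training are plausible candidates.

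**The wording is permissive and the article is condensed.** Saying that potential covariates will be considered does not forbid others, and a full list could sit in an analysis plan that is not shown. But the article states a selection criterion, and that criterion works against the purpose given in Limitations. Permissive wording also means that even a covariate with P<0.01 need not enter.

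**Stronger readings that the documents do not support.** A reader might infer that most real confounders will go unadjusted, or that the P value and interval for the primary outcome are invalid. Both depend on imbalances that the protocol does not give, and a very large imbalance would usually be caught. A reader might also compute the bias as though the confounder were never adjusted: 0.4 × 0.4 = 0.16 SD, with a type I error of about 10%. That is not the stated rule, which admits this confounder about one time in five and leaves about 0.10 SD and 7%.

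**The choice of tests.** The t-test and ANOVA do not suit categorical characteristics such as sex or marital status, and with two groups ANOVA is equivalent to the t-test. This is secondary: it may be condensation, and it falls away if the screening is dropped.

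**A possible misprint.** If 0.1 was meant, a true imbalance of 0.5 SD would pass 72% of the time, but selection would still ignore prognostic strength.

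**Conclusion.** The point holds as a criticism of the selection rule. In a comparison of two recruitment periods, with 40 per group, a P<0.01 screen usually excludes true imbalances below about 0.59 SD and takes no account of prognostic strength. That weakens the adjustment on which the Limitations section relies.

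The entry probabilities follow from the sample size and the threshold alone. The bias of about 0.10 to 0.12 SD and type I error of about 7% to 9%, for imbalances of 0.3 to 0.5 SD with correlations of 0.4 to 0.5, rest on those assumed values, on a single confounder and on a comparison of post-intervention scores. Under a group-by-time contrast including T0 they would apply only to confounders of change. Several confounders acting in the same direction would add to the bias.

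No choice of covariates removes a secular trend, because group and calendar period coincide. The protocol discloses that susceptibility, but it should not present covariate adjustment as a remedy for it.

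**What to change.** - Delete the P<0.01 rule and the baseline significance tests. Describe balance with standardised differences.
- Name a short list of covariates chosen on prognostic grounds from data already collected, and adjust for all of them whatever their baseline P values. Candidates: baseline Autism Behavior Checklist score, child age, time since diagnosis (derivable from age at diagnosis), parent education, income and prior training.
- Handle the baseline outcome once. Either make it a covariate with only T1 and T2 as responses, or keep T0 as a response and read the effect from the group-by-time terms. Doing both uses the same value twice. State which is chosen.
- The stated study period ended in May 2024, so the list may no longer count as prespecified. Record it as a dated change made by analysts blinded to group and outcome results, in keeping with the blinding of analysts promised in Limitations.
- State in Limitations that covariate adjustment cannot remove a secular trend in this design.

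The cost is analysis wording and a few degrees of freedom in about 68 to 80 parents (2 × 34 to 2 × 40). Multi-category education or income would use more than one parameter each, so the list should stay short and the categories coarse. No new data are needed.
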